#### Data management and analysis

Data collection and management will follow Good Clinical Practice (GCP) guidelines and Standard Operating Procedure. Each participant will be assigned a unique ID so that their reported data could be identified. Data cleaning will follow standard procedure, and all the changes will be documented. Findings of this trial will be reported according to the revised CONSORT guidelines [23]. Stata 16.0 will be used for quantitative analyses. Data will be password-protected and only accessible for authorized personnel of the research team. In accordance with good trial practices, data and all related documentation will be stored for a minimum of 7 years after the completion of the trial.

All statistical analyses were performed using STATA version 16.0 for Mac (Stata Corp, College Station, TX, USA). Descriptive statistics will be applied to summarize the socio-demographic and clinical characteristics, as well as the outcome measures for all trial participants at baseline, intermediate and endline. Participants who are loss-to-follow-up will be compared using chi-square tests and t tests to assess the potential bias. The primary outcome analysis will be masked until the analyses is finalized and approved by all researchers. Adequate intervention will be defined as having received a minimum of 12 group sessions. We will not define adequate FBC for the control arm a priori. CBR worker’s characteristics such as educational background, post-training competency and relative working experience will also be described.

Data analysis will be conducted under intention-to-treat assumption. The primary outcome----12-month PANSS total score, adjusted for PANSS scores at baseline and site, and including clustering effects of CBR workers, will be used for examining the comparative effects of intervention and control arm. Personal and social function (PSP score), antipsychotic adherence (MARS score), knowledge of schizophrenia (KAST score) and hospital readmission will be similarly analyzed. A longitudinal analysis including both 6- and 12-month outcomes will also be performed using a GEE or random effects model including an interaction term of time and treatment allowing for modelling changes over time. Long-term outcomes (ADL & IADL, PSSS, EQ-5D, SQLS and BAS score) at 12 months will be analyzed in a similar way to the primary outcome. We will also perform residual analysis to check the data distribution and to detect outliers. Multiple imputation methods will be employed for participants with missing outcome variables.

Several sensitivity analyses are planned to be carried out. First, a complete case analysis and a complier average causal effect will be conducted. Second, a dose-response relationship between adherence to CBR intervention (number of group sessions attended) and the intermediate and long-term outcomes will be examined. Third, we will also conduct data analyses that including received quantity of different CBR modules to identify the active components. Furthermore, regression models will also be re-estimated to include possible confounders such as characteristics of CBR workers and participant characteristics that differ at baseline.

Exploratory subgroup analyses by gender, urban-rural residence, baseline symptom severity and antipsychotic adherence will be completed, although the power for these analyses has not been specifically allowed for.

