#### Allocation

The randomization processes of sub-districts to intervention and control arms are as follows: (1) The sociodemographic characteristics and specific information of patients with schizophrenia of each sub-district will be obtained from the information system [11]; (2) A pairwise matching work will be conducted to identify 9 pairs of matched sub-district that share similar characteristics (number of population, prevalence of schizophrenia, average income per capita, etc.); (3) Within each pair, one sub-district will be randomly assigned into intervention arm, and the remaining one will be assigned into control arm, yielding to 9 sub-districts in intervention arm that providing FBC + CBR, and 9 sub-districts in control arm with FBC only. The sub-district allocation list will be kept securely on a password-protected document by the trial coordinator. To reduce selection bias, the potential eligible participants will not be informed about the allocation of their sub-district until they have consented to participate and baseline data of all participants have been collected. Recruitment and participant flow will be closely monitored by the trial coordinator.

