##### CBR worker recruitment and training

Nineteen CBR workers were recruited from mental health center of the three districts in Weifang city according to the following criteria: (1) at least 12 years of schooling, (2) resident in Weifang city, (3) one-year-or-above working experience related to psychiatry or psychology and (4) interest in community work. CBR training was delivered by multiple sessions at different time (time before delivering new module) to ensure that each intervention module was fully learned and will be smoothly implemented. A intervention manual will be provided for each CBR worker. The competency of CBR workers will then be assessed using role-plays and patient vignettes.

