##### CBR delivery

The CBR intervention will be delivered by group at community health centers. Two CBR workers will be attached to each sub-district and have one group of 10–20 people with schizophrenia. CBR delivery will commence immediately after recruitment into the trial. A total of 18 group intervention sessions will be implemented within the following 12 months, and each group intervention session will last 90–120 min. The intervention is delivered in two phases (Table 1): In phase 1 (intensive engagement phase), 12 intervention sessions will be delivered fortnightly during the first 6 months. The content of the intervention includes a series of modules such as developing a positive therapeutic alliance, understanding schizophrenia, adherence management, etc. (Table 1). In phase 2 (stabilizing phase), 6 intervention sessions will be delivered monthly during the last 6 months. Intervention modules in this phase are similar with phase 1 to reinforce the progress, and the content will include more in-depth discussion and address unmet needs from the first phase. In this phase, a personal rehabilitation plan for each participant will be generated to help their continued rehabilitation at home.

The content and process of the phase specific delivery of the intervention has been manualized. CBR workers will be closely supervised at each site by psychiatrists who will work as designated intervention coordinators. They will coordinate the overall delivery of the intervention and assure the quality and fidelity of the intervention at the site. The treating psychiatrists will provide clinical leadership for the community care teams and ongoing supervision to maintain safety and quality standards.

In total, we anticipate that each participant in the intervention arm will receive a maximum of 18 group-based rehabilitation sessions during the 12 months of the intervention. In evaluating the intervention, a minimum adequate number of 12 sessions attended over 12 months was set according to priori definitions.

**Table 1 Tab1:** CRISC community-based rehabilitation (CBR) intervention outline

phase	months	frequency	Objectives	CBR Modules	CBR activity

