### Quality assurance and fidelity management

To ensure that the CBR intervention is of adequate fidelity, each district will be assigned a coordinator to monitor the delivery of CBR sessions in the three sub-districts from intervention arm every month. The intervention coordinators will record and rate the key contents of the CBR sessions such as interactions between CBR workers and participants, the ways of module presentation, etc., according to a specially designed rating scale. Regular meetings will be held to provide feedback for improving the delivery of the intervention to all CBR workers to maintain quality benchmarks of the trial. Any significant divergence from the intervention manual will lead to suitable corrective action to harmonize the intervention across the sites.

To ensure the adequate quality of outcome measurements in the baseline, intermediate and endline survey, three procedures of supervision will be implemented. First, all the interviews, including both the part of primary care physicians and will be sound recorded (after obtaining the consent of participants), the records will be directly sent to team researchers and experts in psychiatry (for symptoms and function assessment) every day for quality control purpose. Any divergence from the protocol norms will lead to communication with data collectors for correction, and significant errors will lead to re-interview for outcome measurements. Second, each district will be assigned a coordinator to monitor 20% interviews of every sub-district through randomly onsite visits. The coordinator will provide feedback based on a specially designed assessment form to the team researchers. Third, researchers will also conduct casual inspection to check the quality of 10% of the finished questionnaire and assessment through the online platform. The submitted questionnaire will be sent back to data collector for re-check if any illogical error was found. A weekly group meeting with data collectors, researchers and experts in psychiatry will be held to ensure the interview norms and to achieve the overall quality benchmarks.

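### The primary analysis is promised as masked, yet its model names a clustering variable, the CBR worker, that exists only in the intervention arm

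*Protocol article*

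**What the plan says.** All places are in the protocol article.

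- **Masking** (Data management and analysis): "The primary outcome analysis will be masked until the analyses is finalized and approved by all researchers". The article does not say who is masked, or from what.
- **Primary model** (same section): 12-month PANSS total, "adjusted for PANSS scores at baseline and site, and including clustering effects of CBR workers". No other clustering term is named for this model.
- **Control arm** (Allocation): "9 sub-districts in control arm with FBC only".
- **Workers** (CBR worker recruitment and training; CBR delivery): "Nineteen CBR workers were recruited from mental health center of the three districts in Weifang city", and "Two CBR workers will be attached to each sub-district and have one group of 10–20 people with schizophrenia".
- **Where sessions run** (Quality assurance and fidelity management): each district has a coordinator to "monitor the delivery of CBR sessions in the three sub-districts from intervention arm every month".

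The analysis section also plans residual checks for outliers, multiple imputation of missing outcomes, and sensitivity analyses that use sessions attended, quantity of each module received, and CBR-worker characteristics.

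**The concern.** A masked analysis is meant to let data-dependent decisions be settled before anyone can tell which arm they favour. In this plan the decisions on the primary outcome that masking would protect are how outliers are treated and how missing PANSS scores are imputed. Both act on the real data, and the data used to fit the stated model must carry its clustering field.

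That field is the CBR worker, and a control participant has none. A variable that is defined in one arm only marks the arm. The plan therefore claims a safeguard and then specifies a model whose own input can undo it. A reader of the eventual report would credit the trial with protection that the written plan does not secure.

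**Working it through.** No figure in the plan has to be reproduced here, because the point does not rest on sample size, power or alpha. The check is where CBR workers can exist, and what follows for the analysis file.

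**1. Number of sub-districts with CBR sessions.** There are three intervention sub-districts per district and three districts: 3 × 3 = 9. This agrees with the 9 sub-districts allocated to each arm.

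**2. Worker count.** The delivery section attaches two workers to each sub-district without saying whether that covers all 18 or only those with CBR.

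| Reading | Workers needed | Recruited |
|---|---|---|
| Intervention sub-districts only | 2 × 9 = 18 | 19 |
| All sub-districts | 2 × 18 = 36 | 19 |

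Only the first reading fits, with one worker to spare. The count is supporting evidence. The decisive facts are that control sub-districts receive facility-based care alone and that the sessions monitored are those in intervention sub-districts. Worker identity is therefore an intervention-arm variable.

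**3. What the field looks like for controls.** The article gives no value. The obvious codings are:

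- blank for all controls: blank means control;
- one dummy worker for all controls: the dummy value appears in all 9 control sub-districts and in no intervention sub-district;
- each control as a cluster of one: singletons mean control, because intervention patients are in groups of 10–20.

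Each coding separates the arms completely. This holds only if the file contains the field in that form.

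**4. A coding that does not reveal the arm.** Each intervention sub-district has one group and one pair of workers, so worker pair and sub-district coincide there. A clustering field of 18 randomly assigned sub-district codes, 9 per arm, covers the same groups, is defined for controls, and does not by its form show the arm. It is, however, a different term from the one the model names.

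**5. Other one-arm fields.** Sessions attended, module quantities and worker characteristics also exist only for the intervention arm. They are needed for the complier, dose-response, module and adjusted sensitivity analyses, not for the primary model. The article does not say that they are held back from the primary file.

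**The case against.** The strongest reply is that the article leaves open how masking is carried out. Coded labels, a separate unmasked programmer, or finalising the code on a dummy allocation would each be ordinary practice, and a journal article commonly leaves such detail to the full protocol or SAP. The word masked might also mean only that results are withheld until approval. Most of this stands: the absence of operational detail is no fault. It does not remove the conflict, because the clustering term actually named is the one that works against masking. Code written on a dummy allocation would still have to be followed by outlier checks and imputation on real data.

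A reader might infer more than the documents support:

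- **That analysts will see every participant's arm.** Nothing says that analysts receive raw worker identity. The statement is conditional on the contents of the file.
- **That the researchers who approve the analysis know the allocation.** The article records "A weekly group meeting with data collectors, researchers and experts in psychiatry will be held", but the stated purpose is interview standards and data quality. The allocation list is held under password by the trial coordinator. Knowledge among approvers is plausible but not documented.
- **That the type I error rises by some amount.** The document gives no basis for a figure. Keeping the more extreme of several specifications is equally possible with arms labelled A and B, so such inflation would measure free choice of model and not loss of masking.
- **That many primary-model choices are open.** The GEE or random-effects choice belongs to the additional longitudinal analysis, and covariates that differ at baseline belong to the sensitivity models. The primary covariates are fixed as baseline PANSS and site.

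**Conclusion.** The point holds in conditional form. The masking statement and the primary model are in conflict because the clustering variable named exists in 9 of the 18 sub-districts only. If the analysis file carries it as written, it separates the arms during the outlier and imputation decisions, and the masking is not secured. Whether this will happen cannot be told from the article.

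The conclusion assumes that masked refers at least to treatment arm and that workers have no role in control sub-districts, which the control-arm description and the worker count (18 needed for nine sub-districts, 19 recruited) both support.

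This is a minor point, worth making because it is specific and cheap to correct. The same sentence raises a separate and larger statistical matter: the clustering term has no definition for controls, and the randomised sub-district is not named in the model. The first step of the fix deals with the clustering term for both purposes.

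**What to change.** In Data management and analysis:

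1. **Primary model.** Replace the CBR-worker term with the randomised sub-district, defined in both arms. This must come first: taking worker codes out of the file without naming a replacement would leave the stated model impossible to fit.
2. **Masking statement.** Say that the primary-analysis file carries only random codes for arm (A/B), sub-district, matched pair and site, and that outlier and imputation decisions are settled on that file. The trial coordinator already holds the allocation list and could issue it.
3. **Held-back data.** Merge worker identity, worker characteristics, attendance and module counts, and release the arm labels, only after the primary result is locked.
4. **Otherwise**, delete the statement that the primary analysis is masked.

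The cost is a recoding step and a few sentences, with no extra staff or data. The downside is small: worker-level, complier, dose-response and module analyses start later.

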## Methods

### Study design

The design is a cluster randomized controlled trial with sub-district as the unit of randomization. There are mainly three reasons for choosing cluster randomization as the method of randomization: (1) CBR was provided as group intervention at community healthcare, which exclude the possibility of randomization at individual level; (2) randomization at sub-district will be more economical and less time-consuming for both provider and participants; (3) The acceptability will be maximized, and the possibility of contamination could be minimized if all participants in a sub-district are allocated to either intervention or control arms. The study flow chart is presented in Fig. 1. Eighteen sub-districts from three district in Weifang, Shandong province were included for the trial, 9 will be randomly allocated to the intervention arm (FBC plus CBR) and 9 randomly allocated to the control arm (FBC alone). In total, 334 participant dyads (patients and their caregivers) will be recruited, with 18.6 participant dyads on average recruited for each sub-district.

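### The primary model names CBR workers as the clustering unit; they serve only the intervention arm, so clustering within the 9 randomised control sub-districts is left out

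*Protocol article*

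**What the plan says.** Under Study design the article states: "The design is a cluster randomized controlled trial with sub-district as the unit of randomization". Allocation describes how the 18 sub-districts are matched to "identify 9 pairs of matched sub-district that share similar characteristics", and then: "Within each pair, one sub-district will be randomly assigned into intervention arm, and the remaining one will be assigned into control arm". The result includes "9 sub-districts in control arm with FBC only".

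Under CBR delivery: "Two CBR workers will be attached to each sub-district and have one group of 10–20 people with schizophrenia". Nothing attaches a CBR worker to a control sub-district.

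Under Data management and analysis, the 12-month PANSS total score is to be "adjusted for PANSS scores at baseline and site, and including clustering effects of CBR workers". PSP, MARS, KAST and readmission are analysed likewise, and the long-term outcomes in a similar way. No section puts the sub-district or the matched pair into a model, and the word site is not defined. A later sensitivity analysis would refit the regressions to "include possible confounders such as characteristics of CBR workers and participant characteristics that differ at baseline".

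**The concern.** In a cluster trial the analysis must reflect the unit that was randomised. The article does not leave this to a later document: it names a clustering unit, and it is a different one. That unit exists in one arm only. A control participant has no CBR worker, so the stated term says nothing about correlation among patients of the same control sub-district, although each sub-district has its own community health centre and its own primary care physicians, who collect most outcomes.

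If control patients are handled as independent observations, the variance of the control mean is understated, and with it the standard error of the treatment effect. The primary PANSS test, and every outcome analysed in the same way, would then reject too often under the null.

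**Working it through.** **Inputs.** 9 sub-districts per arm (Allocation). Mean cluster size m: 220/18 = 12.2 (evaluable), 264/18 = 14.7 (Sample size estimation) and 334/18 = 18.6 (Study design). The article gives both 264 and 334 as the recruitment total, so the whole range is shown. ICC 0.05 and alpha 0.05 (Sample size estimation); the ICC is stated for districts, so using it for sub-districts is an assumption, and a two-sided test is assumed. The article's only type I error figure is the nominal 0.05.

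**What the worker term covers.** Two workers share one group in each intervention sub-district, so in that arm a worker-pair effect is a sub-district effect. Nothing comparable exists in the control arm.

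**Analytic check, controls independent.** DEFF = 1 + (m − 1) × ICC. The true variance of the arm difference is proportional to 2 × DEFF; the model uses DEFF + 1. SE ratio = √[(DEFF + 1)/(2 × DEFF)]; actual alpha = 2 × [1 − Φ(1.96 × SE ratio)].

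| m | DEFF | SE ratio | Actual alpha |
|---|---|---|---|
| 12.2 | 1.56 | 0.91 | 0.076 |
| 14.7 | 1.68 | 0.89 | 0.080 |
| 18.6 | 1.88 | 0.88 | 0.086 |

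The same formula gives 0.062 to 0.068 at ICC 0.02 and 0.093 to 0.106 at ICC 0.10.

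**Simulation.** Null trials, 9 v 9 clusters of 12, 15 or 19, 10,000 runs per cell, no baseline, site or pair adjustment, estimated between-cluster variance not allowed below zero. Cells show type I error for m = 12 / 15 / 19.

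| ICC | Intervention arm clustered, normal reference | Same, Satterthwaite df | Sub-district means, t on 16 df |
|---|---|---|---|
| 0.02 | 0.061 / 0.065 / 0.070 | 0.050 / 0.054 / 0.056 | 0.051 / 0.050 / 0.048 |
| 0.05 | 0.079 / 0.088 / 0.098 | 0.065 / 0.072 / 0.079 | 0.049 / 0.051 / 0.049 |
| 0.10 | 0.099 / 0.116 / 0.126 | 0.079 / 0.093 / 0.103 | 0.044 / 0.049 / 0.050 |

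A repeat with 40,000 runs, without that floor on the variance, gives at ICC 0.05 0.087 / 0.096 / 0.103 (normal) and 0.072 / 0.080 / 0.085 (Satterthwaite). At ICC 0.02 it gives 0.073 to 0.078 and 0.063 to 0.066.

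**Other codings of the controls.** The article does not say how controls enter a worker-clustered model.
- All controls as one cluster, with cluster-robust standard errors: simulated type I error about 0.15.
- All controls as one cluster in a random-intercept model: the standard error is too large. With 264/2 = 132 per arm, total variance 1 and ICC 0.05, the model variance is 0.05/9 + 0.05 + 2 × 0.95/132 = 0.0700. The true variance is 2 × 1.683/132 = 0.0255. The SE ratio is √(0.0700/0.0255) = 1.66.

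**Does site repair it?** As a district effect it leaves sub-district variation within districts. As a fixed sub-district effect it is collinear with arm, so the treatment effect cannot be estimated. As a random sub-district effect it would work, but the article does not say that.

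**The case against.** Several points on the other side are fair.

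- Half of the randomised units are in effect represented, because worker pair and sub-district coincide in the intervention arm. This stands, and confines the omission to the control arm.
- A reader might infer that type I error is doubled. It approaches 10% at ICC 0.05 only with the larger clusters and a normal reference, which the article does not prescribe. Part of that excess is a small-sample problem: correct sub-district means tested against a normal reference already give about 7%. With Satterthwaite degrees of freedom the range is 6.5 to 8.5%.
- A reader might go further and quote the error for ignoring clustering in both arms (12 to 15% analytically at ICC 0.05). The article describes no such model.
- A reader might conclude that no positive result could be trusted. With SE ratios of 0.875 to 0.906, a reported p below about 0.025 to 0.030 stays under 0.05 after correction on a normal reference (1.96/0.875 = 2.24; 1.96/0.906 = 2.16). Using the 16 df quantile (2.120) the limit is about 0.015 to 0.019. Only results nearer the threshold would change.
- Baseline PANSS and site adjustment could lower the residual ICC. This stands: at ICC 0.02 with Satterthwaite degrees of freedom the error is only 5 to 6.6%.
- Leaving out the matched pairs is not a source of this inflation; ignoring effective matching tends to be conservative.

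None of this makes the stated clustering unit the right one.

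**Conclusion.** The sentence is wrong as written. It names a clustering unit that is not the randomised one and has no meaning in the control arm, and only an unstated reading of site would rescue it. If controls are treated as independent and the sub-district ICC is 0.05, type I error is about 7 to 10% instead of 5%, against about 5% for a sub-district analysis on 16 df. The size depends on the ICC, the cluster size, the reference distribution and the covariate adjustment.

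It would be too strong to say that standard errors are certain to be too small: that depends on how controls are coded, and one plausible coding makes them too large. That a single sentence permits errors in both directions is itself a reason to rewrite it. The fault carries over to the outcomes analysed in the same way.

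A secondary point concerns a sensitivity analysis only and does not touch the primary test: CBR-worker characteristics have no value in the control arm, so a two-arm model cannot adjust for them.

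**What to change.** Replace the CBR-worker clustering term with a random intercept for sub-district in both arms, or use a cluster-level analysis. Adjust for baseline PANSS and district, naming district in place of site. Use a small-sample degrees-of-freedom correction for 18 clusters, and state how the matched pairs enter. The 5% shown above is for unmatched sub-district means on 16 df; the mixed model with pairs was not simulated, and a paired comparison of 9 pairs would have 8 df.

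Use the same clustering unit in the 6- and 12-month model and for the other outcomes, with a suitable model for readmission if it is binary. In the sensitivity analyses, drop CBR-worker characteristics from two-arm models and describe them within the intervention arm.

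The cost is wording, with no new data. The confidence interval becomes somewhat wider: at ICC 0.05 by a factor of 1/0.906 = 1.10 to 1/0.875 = 1.14 from the standard error, and by a further 2.120/1.960 = 1.08 if a normal reference would otherwise have been used and 16 df apply.

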### Setting

The trial will take place in Hanting, Kuiwen and Weicheng district, Weifang city, Shandong province in China. The three districts have a population of 1,470,000 persons in 23 sub-districts. Six sub-districts in each district were chosen, yielding to 18 sub-districts in the trial. There is a community health center in each sub-district that covering the facility-based care of local people with severe psychiatric disorders including schizophrenia. The number of registered schizophrenia patients of each sub-district ranges from 52 to 138, with 12 to 25 patients are planned to recruit.

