### Statistical issue

#### Sample size estimation

Based on the data from the earlier random controlled trials [9, 21], it was assumed that the participants in the intervention arm will have 20% reduction on the PANSS total score mean reduction after the 12-months CBR, and there was no change observed for participants in the control arm. The intra-class correlation within the three districts was set at 0.05 and alpha was set as 0.05. Based on methods from previous literature [22], a sample size of 110 participants in both intervention arm control arm was calculated for this trial, which will give us 90% power to detect the difference. The required sample size of 220 was increased to 264 to allow for 20% attrition. The total number of participants will be divided slightly unequally between sub-districts for reasons of feasibility.

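### The longitudinal model behind the 6-month objectives may be an ordinary GEE not tied to the 18 randomised sub-districts, and such a GEE would be anti-conservative

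*Protocol article*

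**What the plan says.** Study design (Protocol article): "The design is a cluster randomized controlled trial with sub-district as the unit of randomization". The same section gives the numbers: "9 will be randomly allocated to the intervention arm (FBC plus CBR) and 9 randomly allocated to the control arm (FBC alone". Under Setting, the planned recruitment per sub-district is given as "with 12 to 25 patients are planned to recruit".

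Data management and analysis describes two kinds of model. The primary one compares 12-month PANSS total between arms, adjusted for baseline PANSS and site, and allows for clustering by CBR worker. PSP, MARS, KAST and readmission are to be handled in a similar way. The text then adds a longitudinal analysis of the 6- and 12-month outcomes "using a GEE or random effects model including an interaction term of time and treatment". For this second model it gives no clustering level, variance estimator or reference distribution.

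Under Objectives, the secondary objectives (adherence, readmission, knowledge of the illness) are each set at 6 and at 12 months. The longitudinal sentence is the only treatment comparison in the analysis section that names the 6-month data.

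**The concern.** Everyone in a sub-district is allocated together, so the information about the treatment effect is limited by 18 sub-districts, not by the number of participants. Two ordinary ways of running a longitudinal GEE would not respect this.

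- **Clustered on sub-district, usual sandwich variance, normal reference.** The sandwich variance relies on many clusters. With 9 per arm it is biased downwards, and 1.96 is too small a critical value.
- **Clustered on participant only.** This accounts for the repeated measures within a person but ignores the sub-district. It is an easy default in a longitudinal model when the text names no cluster.

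The wording elsewhere does not settle which is meant. The one clustering level named is the CBR worker, and CBR workers deliver only the intervention, so that level gives control sub-districts no clusters. At stake are the 6-month results and the statements about change over time: intervals that are too short, and effects declared too often.

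**Working it through.** **The plan's own figure.** The article gives no interval width or error rate for the longitudinal model, so there is nothing to reproduce. Its sample size figures do not bear on this point.

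**Inputs from the Protocol article.** There are 18 sub-districts, 9 per arm. Cluster size is 12 to 25 (Setting). The mean is 264/18 = 14.7 from the Sample size estimation total, or 334/18 = 18.6 from the Study design total. For the ICC: "The intra-class correlation within the three districts was set at 0.05 and alpha was set as 0.05". That value is stated for districts; applying it to sub-districts is an assumption, so 0.01 to 0.10 is also shown.

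**Step 1: critical value alone.** With 18 - 2 = 16 degrees of freedom, t = 2.120 against 1.960. The ratio is 2.120/1.960 = 1.08, so the t interval is about 8% wider. A z test applied to a statistic that truly follows t with 16 df rejects 6.8% of the time, before any sandwich bias.

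**Step 2: simulation with no treatment effect.** There were 2,500 trials per ICC, with 18 clusters of 12 to 25, allocated 3 v 3 in each of three districts. Outcomes were at 6 and 12 months. The model was an independence-working GEE with time, arm effect at each time, baseline and site; the 12-month arm effect was tested at two-sided 5%. Assumptions: normal data, half of the within-cluster variance due to the participant, baseline coefficient 0.6, matched pairs not modelled.

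| Rejection rate | ICC 0.01 | ICC 0.05 | ICC 0.10 |
|---|---|---|---|
| Sub-district sandwich, z | 9.6% | 11.1% | 10.6% |
| Same, scaled by 18/17, z | 8.8% | 10.3% | 9.6% |
| Same as row 1, but t with 16 df | 7.6% | 8.4% | 8.3% |
| Kauermann-Carroll, t with 16 df | 5.0% | 5.4% | 4.8% |
| Mancl-DeRouen, t with 16 df | 2.9% | 2.9% | 2.6% |
| Participant sandwich, z | 6.6% | 16.4% | 25.2% |

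Monte Carlo standard error at 11.1% is √(0.111 × 0.889/2500) = 0.6 percentage points. A nominal 95% interval from row 1 covers about 89-90%.

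**Step 3: a second simulation with smaller clusters.** With 10 to 20 per sub-district, ICC 0.05, two time points, and baseline and site adjustment, the rates were about 11% (sub-district sandwich, z), about 14% (participant only) and about 5% (sub-district-level t test).

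**Step 4: check of the participant-only figures by formula.** Ignoring the sub-district understates the variance by the design effect 1 + (m - 1) × ICC, so the rejection rate is roughly 2 × [1 - Φ(1.96/√DE)].

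- m = 18.5: DE = 1 + 17.5 × 0.05 = 1.875, and 1.96/1.369 = 1.43, which gives 15.2% (simulated 16.4%).
- m = 15: DE = 1 + 14 × 0.05 = 1.70, and 1.96/1.304 = 1.50, which gives 13.3% (simulated about 14%).

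The formula assumes equal cluster sizes, which fits its slightly lower values. The difference between 14% and 16% is mainly a matter of cluster size.

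**Step 5: dependence on the model.** A simpler single-time-point simulation (ICC 0.05, size CV 0.2) gave 7.9% at 14.7 per sub-district and 8.7% at 18.6 for the uncorrected z test, and 4.5-5.1% for a sub-district-level t test. The direction is the same. The two-time-point figures are closer to the model in the protocol and are the ones used here.

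**The case against.** The strongest reply is that the article is silent here, not wrong. Variance estimators and degrees of freedom are commonly left to a full protocol or SAP, and neither is shown. The inflation arises only if GEE is chosen and then run in its ordinary form. This stands in part: a reader might infer that the plan commits to an uncorrected GEE, and the text does not say that.

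What keeps the point alive is what the article does say. It offers GEE as an accepted option in a trial with 9 clusters per arm, and the only clustering level it names is not the randomised unit. A reader therefore cannot assume that the sub-district will be the cluster in the longitudinal model.

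A reader might also infer that the trial's main result is compromised. It is not: the longitudinal analysis is additional, and the 12-month PANSS comparison is a separate model. Whether clustering by CBR worker suits that primary model is a different question, which this sentence does not decide.

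It may be argued that outcomes handled similarly to the primary one would also be analysed that way at 6 months. The text does not say so; the model they follow is a 12-month one.

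Lastly, a linear mixed model does not suit hospital readmission if it is analysed as binary. This is correct, and the fix keeps GEE available for that case.

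**Conclusion.** The point holds in conditional form. The article leaves the model that carries the 6-month objectives open between two methods, neither tied to the sub-district. If an ordinary GEE were used, nominal 5% tests would reject about 10-11% of the time with an uncorrected sandwich z test clustered on sub-district, fairly steadily over ICC 0.01-0.10. Clustered on participant only, they would reject about 14-16% of the time at ICC 0.05, and anywhere from 6.6% to 25.2% over ICC 0.01-0.10. A Kauermann-Carroll variance with a t reference brings the rate back to about 5%.

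These figures rest on normal outcomes, the stated ICC carried over from districts to sub-districts, and pairs left out of the simulation. They were not computed for a binary outcome or for the random effects option. The exposure is the 6-month effects and change over time, not the 12-month primary comparison.

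**What to change.** Replace the open choice with a specification for each type of outcome.

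- **Continuous scales (PANSS, PSP, MARS, KAST):** a linear mixed model with random effects for sub-district and participant, the matched pairs reflected in the model, time as a factor, arm-by-time terms and Kenward-Roger degrees of freedom. Report the arm effect at 6 months and at 12 months.
- **Wherever GEE is used, including readmission if binary:** cluster on sub-district, use a bias-corrected variance such as Kauermann-Carroll, and take the t reference with degrees of freedom based on the number of clusters.

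This changes analysis wording only, with no new data and no change in conduct; Stata 16, the package named, fits this mixed model. The price is somewhat wider intervals. From the critical value alone they are about 8% wider with 16 degrees of freedom. If the analysis were based on the 9 pairs (9 - 1 = 8 degrees of freedom, t = 2.306), they would be 2.306/1.960 = 1.18, or about 18% wider, before any gain in precision from the matching. The variance correction adds to this.
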